## Abstract

**Background:**

Pain after major head and neck cancer surgery is underestimated and has both nociceptive and neuropathic characteristics. Extended resection, flap coverage, nerve lesions, inflammation, and high-dose opioid administration can also lead to hyperalgesia and chronic postoperative pain. Opioids are frequently associated with adverse events such as dizziness, drowsiness, nausea and vomiting, or constipation disturbing postoperative recovery and extending the length of hospital stay. Patients eligible for major head and neck cancer surgery cannot benefit from full multimodal pain management with locoregional anesthesia. Intravenous lidocaine, investigated in several studies, has been found to decrease acute pain and morphine consumption. Some data suggest also that it can prevent chronic postsurgical pain. Evidence supporting its use varies between surgical procedures, and there is no published study regarding systemic lidocaine administration in major head and neck cancer surgery. We hypothesized that intravenous lidocaine infused in the perioperative period would lead to opioid sparing and chronic postsurgical pain reduction.

**Methods/design:**

A total of 128 patients undergoing major head and neck surgery will be included in this prospective two-center, double-blind, randomized controlled trial. Patients will be randomly assigned to lidocaine or placebo treatment. After induction of general anesthesia, an intravenous lidocaine bolus will be administered (1.5 mg.kg^− 1^), followed by a continuous infusion (2 mg.kg^− 1^.h^− 1^) which will be reduced in the postanesthesia care unit (1 mg.kg^− 1^.h^− 1^). The primary outcome measure is morphine consumption 48 h after surgery. The secondary outcomes include intraoperative remifentanil consumption, morphine consumption 24 h after surgery, and chronic postsurgical pain that will be assessed 3–6 months after surgery.

**Discussion:**

Recent evidence suggests that intravenous lidocaine can lead to opioid sparing and chronic postsurgical pain reduction for certain types of surgery. This is the first trial to prospectively investigate the efficacy and safety of intravenous lidocaine in major head and neck cancer surgery.

**Trial registration:**

ClinicalTrials.gov, NCT02894710. Registered on 11 August 2016.

**Electronic supplementary material:**

The online version of this article (10.1186/s13063-019-3303-x) contains supplementary material, which is available to authorized users.

## Background

Intravenous lidocaine has spurred an increased interest in the use of alternative perioperative nonopioid analgesia after major surgery [1]. Morphine has long been considered the gold standard to relieve pain after most surgical procedures. However, opioid-related adverse events, such as postoperative nausea and vomiting (PONV), constipation, itching, sedation, drowsiness, dizziness, and respiratory depression, may disturb postoperative recovery and extend the length of hospital stay. Furthermore, neuronal activation and central neuroplasticity generated by intense nociceptive stimulation and high-dose opioid administration can result in hyperalgesia and chronic postsurgical pain (CPSP) [2]. Thus, opioid sparing by an antihyperalgesic compound such as lidocaine could prevent CPSP [3–5]. Systemic lidocaine, used initially as an antiarrhythmic drug, has a very short half-life and a favorable safety profile for systemic administration [6]. Through its analgesic and anti-inflammatory activities, systemic lidocaine enhances postoperative recovery by opioid sparing and by reducing immune alterations [7]. A recent meta-analysis found that the efficacy of perioperative intravenous lidocaine for postoperative pain varies between surgical procedures [8]. Indeed, opioid sparing was observed after lidocaine infusion in open abdominal [9, 10] and laparoscopic [11, 12] procedures, thyroid surgery [13], and cardiac [14], thoracic [15], and major spine [16] procedures. Moreover, data suggest a reduction of CPSP development in breast surgery [4, 17]. The published data being inconsistent, the efficacy of lidocaine infusion has to be assessed for each surgical procedure. There is no published study that has evaluated intravenous lidocaine in major head and neck cancer surgery. In these procedures, acute and CPSP are major and underestimated issues [18–20]. Patients are not eligible for a full multimodal pain management with locoregional anesthesia. The head and neck region is widely innervated. Erosive tumor, inflammation, and extended surgical resections can lead to acute postoperative pain that has various characteristics (nociceptive, neuropathic, and psychological). Insufficient pain relief, nerve lesions, and high opioid consumption can result in hyperalgesia and chronicization of the pain. We hypothesized that perioperative intravenous lidocaine would lead to opioid sparing and CPSP reduction, and therefore designed a study to investigate this, the protocol of which is reported herein.

## Methods/design

### Study design

This study is a two-center, double-blind, randomized controlled prospective trial. It was approved by the local ethics committee (CPP Sud-Est II) on July 6, 2016, and by the French medicines agency (Agence nationale de sécurité du médicament et des produits de santé (ANSM)) on July 7, 2016. The trial is registered on EUDRA-CT (2015-005799-90) and on clinicaltrials.gov (NCT02894710). The trial design is illustrated in Figs. 1 and 2.

**Fig. 1 Fig1:**
[figure not shown]
Flow chart of the study. BMI body mass index, CPSP chronic post-surgical pain, LVEF left ventricular ejection fraction, PT prothrombin time

**Fig. 2 Fig2:**
[figure not shown]
Schedule of study assessments and evaluations. CPSP chronic postsurgical pain, ECG electrocardiogram, NRS numeric rating scale, PACU postanesthesia care unit

### Population

All patients scheduled for elective major head and neck cancer surgery at the Croix-Rousse Hospital (Hospices Civils de Lyon, France) and the Centre Léon Bérard (Lyon, France) will be included after written informed consent is obtained.

### Inclusion criteria

Participants meeting the following criteria will be included: patients undergoing major head and neck cancer surgery (total or partial laryngectomy, crico-hyoido-epiglotto-pexy, oropharyngectomy with or without mandibulotomy, partial pharyngectomy, intraoral extended resection, extended pelvectomy, pelvi-glossectomy with or without pectoralis major flap or free flap with or without cervical lymphadenectomy) and patients receiving standardized morphine patient-controlled analgesia (PCA) in the postoperative period.

### Non-inclusion criteria

Participants meeting one or more of the following criteria will be excluded: refusal to give consent; hypersensitivity to amide local anesthetics; hepatocellular insufficiency (international normalized ratio > 1.6) or cirrhosis; systolic heart failure (left ventricular ejection fraction < 50%); atrioventricular conduction disorders requiring permanent electrosystolic stimulation with pacemaker not yet implemented; treatment with antiarrhythmic or beta-blockers classified by Vaughan Williams; body mass index > 30 kg.m^− 2^; patient already treated for chronic pain with a level 3 analgesic or for neuropathic pain; epilepsy not controlled by treatment; acute porphyria; fluid overload; hypersensitivity to any component of 5% glucose solution; pregnant or lactating women; and patient under legal protection measure.

### Randomization

Patients will be allocated by randomized complete block design, stratified by center, to one of the two groups that will receive either intravenous lidocaine (study group) or placebo (placebo group) during the intraoperative and early postoperative period. The randomization will be processed by the investigator after the preoperative assessment, using a computer-generated list. Allocation concealment will be transmitted to the data manager and to each pharmacy department. Allocation will be ensured by enclosing the treatment unit in sealed, opaque, sequentially numbered envelopes prepared by the pharmacy department, which will be opened only upon arrival of the patient in the operation room by a nurse who will prepare the syringes. The nurse will prepare the treatment unit away from the operating room in order to keep the study participants blinded from the allocation. Preparations will consist of two 50-ml syringes for continuous infusion by syringe pump. Postoperative outcomes will be assessed by research personnel who will remain blinded to the type of intervention throughout the study.

### Intervention plan

For all patients, a standardized general anesthesia and postoperative care protocol will be followed in each center. Anesthesia is performed by the staff anesthesiologist, who does not participate in postoperative evaluation and who is blinded to the patient’s allocation.

### Induction and maintenance of anesthesia

After preoxygenation, anesthesia will be induced by a bolus injection of propofol and an intravenous infusion of remifentanil (Minto model for remifentanil target-controlled infusion adapted to arterial pressure and heart rate variations). Tracheal intubation may be facilitated with a neuromuscular blocking agent according to the clinicians’ decision. Patients will be mechanically ventilated with a mixture of air, oxygen, and sevoflurane. It may be noted that antihyperalgesic agents, such as nitric oxide, ketamine, or nonsteroidal anti-inflammatory drugs, are not allowed during the protocol [21–23]. In all patients, standard monitoring will be applied, including electrocardiogram, pulse oximetry, capnography, and temperature measurements.

### Interventional treatment

In the study group, at the end of the induction of general anesthesia, a bolus of 1.5 mg.kg^− 1^ of intravenous lidocaine will be administered, followed by a continuous infusion of intravenous lidocaine at 2 mg.kg^− 1^.h^− 1^. The lidocaine infusion will be reduced to 1 mg.kg^− 1^.h^− 1^ in the postanesthesia care unit (PACU) and will be discontinued at the time of discharge. The placebo group will receive, in the perioperative period, a placebo infusion with 5% glucose solution at a rate comparable to that of the lidocaine infusion in the study group.

### Postoperative analgesia

Irrespective of group allocation, all patients will receive a combination of intravenous analgesics 30 min before the end of surgery: acetaminophen 1 g and morphine 0.15 mg.kg^− 1^. The patients will be transferred to the PACU for continuous monitoring of vital signs. The Aldrete score will be recorded before leaving the PACU [24]. The level of pain will be assessed using a numeric rating scale (NRS: 0 = no pain, 10 = worst pain you can imagine). As soon as the NRS score exceeds 3, patients will receive a 2 mg intravenous bolus dose of morphine every 10 min [25]. Morphine titration is performed until pain relief. Afterward, the morphine PCA pump will be programmed in an on-demand-only mode without a basal rate, allowing a bolus injection of 1 mg every 7 min without a maximum programmed dose. Patients will be discharged from the PACU only once the Aldrete score is 9, and once there is no evidence of pain and/or PONV.

### Postoperative management

Patients will receive intravenous analgesia with acetaminophen 1 g every 6 h and morphine PCA during at least the first 48 h after the procedure. The fluid balance, enteral nutrition, antibiotic use, and thromboembolic prevention will be at the clinicians’ decision.

### Follow-up visits

The first follow-up visit will be processed in the PACU for assessment of morphine consumption and adverse effects. Two other visits are planned at day 1 and day 2 of the early postoperative period for morphine consumption assessment. The last visit will be 3–6 months after surgery to evaluate CPSP with the NRS and the shortened version of the “Questionnaire Douleur Saint-Antoine” (QDSA), which is the French adaptation of the McGill Pain Questionnaire (MPQ) [26]. Each new analgesic or anti-inflammatory drug or any relevant therapy (such as chemotherapy, radiotherapy) will be noted.

### Primary outcome

The primary outcome is the cumulative administered morphine consumption in the first 48 postoperative hours.

### Secondary outcome

Secondary outcomes include: cumulative remifentanil consumption during surgery; cumulative morphine consumption in the first 24 postoperative hours; assessment of CPSP 3–6 months after surgery using the shortened version of the QDSA; and occurrence of adverse events.

### Assessment of safety

The interventional treatment will be administered to patients with standard hemodynamic monitoring in the setting of a fully equipped operation theater. This enables immediate detection and treatment of adverse events. Administration of study drug will be immediately stopped in cases when the study participant shows a relevant deterioration. Also, after leaving the operation room, all patients will be closely monitored for the occurrence of adverse events, first in the PACU and later in the surgical ward. Moreover, the inclusion of each patient into the study will be noted in the electronic hospital information system and is hence visible to all physicians and nurses involved in the care of the patient. This facilitates reporting of severe adverse events to the principal investigator. The principal investigator will report suspected unexpected serious adverse reactions to the national health authorities.

### Data analysis

Data will be analyzed according to the intention-to-treat principle. Unblinding is planned at the end of the study, after a database freeze. A descriptive analysis will first be performed. The data will be presented as counts and percentages for qualitative data, as means and standard deviation for normally distributed quantitative data, or as medians and interquartile range for non-normally distributed variables. The analysis of the main outcome (cumulative morphine consumption in the first 48 postoperative hours) will be performed using Student’s *t* test. A multivariate linear regression analysis will also be performed to identify factors independently associated with morphine consumption 48 h after surgery. The factors studied will be the type of surgery, tumor site, stage of cancer, duration of the surgery, NRS score upon arrival in the PACU, use of preoperative analgesic, and use of high-dose intraoperative remifentanil. During surgery, intraoperative remifentanil consumption as well as morphine consumption in the 24 postoperative hours will be compared between the two groups using Student’s *t* test. The incidence of postoperative chronic pain will be compared between the two groups and the factors potentially associated with the occurrence of chronic pain will be analyzed by logistic regression. Subgroup analysis will be performed to compare patients with and without major pectoralis flap or free flap. The statistical analyses will be carried out under the responsibility of the methodologist of the clinical research center of the Croix-Rousse Hospital. All analyses will be conducted using SPSS software version 19.0 (IBM Corp., Armonk, NY, USA) and R software (R Development Core Team, Vienna, Austria). A value of *p* < 0.05 will be considered statistically significant.

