### Limits

The study does, however, have several limitations. One limitation is the recruitment of patients undergoing various types of procedure. Surgical techniques will be obviously different according to each procedure, and therefore we have planned subgroup analyses (with or without major pectoralis flap or free flap). Another limitation is that, for organizational issues, treatment units have to be prepared by a PACU nurse who then brings the syringe to the operating theater but who will not be involved in the care of the study patient. Although this aims to guarantee blinding, as the nurse and the medical team treating the patient will be in the same department then a bias due to unblinding cannot be ruled out. Furthermore, if use of postoperative corticosteroids was expected by the surgical team, the patient was not enrolled. However, if corticosteroids are infused in the perioperative period because of a potential upper airway edema, the patient will not be excluded; analyses conducted according to the intention-to-treat principle will be used for analysis, and sub-group analysis will be considered according to each group’s workforce.

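### The intention-to-treat rule is stated for all data and does not exempt adverse events, so any randomised patient who is never infused slightly dilutes the comparison of infusion-related harm

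*Protocol article*

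**What the plan says.** The Data analysis section begins: "Data will be analyzed according to the intention-to-treat principle". It names no outcome to which this does not apply. The Limits section returns to the principle when it discusses perioperative corticosteroids ("analyses conducted according to the intention-to-treat principle will be used for analysis"), again without naming a treated or safety set.

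The Secondary outcome list ends with "and occurrence of adverse events", and the Discussion paragraph of the abstract presents safety as an aim: "This is the first trial to prospectively investigate the efficacy and safety of intravenous lidocaine in major head and neck cancer surgery".

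Three statements fix the timing:

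- Randomization section: "The randomization will be processed by the investigator after the preoperative assessment, using a computer-generated list".
- Same section, on the envelopes holding the treatment unit: "which will be opened only upon arrival of the patient in the operation room by a nurse who will prepare the syringes".
- Interventional treatment section: the bolus is given "In the study group, at the end of the induction of general anesthesia".

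The Assessment of safety section describes surveillance after theatre: "all patients will be closely monitored for the occurrence of adverse events, first in the PACU and later in the surgical ward".

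**The concern.** Randomisation comes before the first dose, with an interval whose length the article does not state. An operation that is cancelled or changed in that interval leaves a patient randomised but not infused. Read as written, the rule keeps this patient in the assigned arm for every outcome, adverse events included.

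For morphine consumption that is the right choice, since dilution makes an efficacy claim harder to reach. For a harm caused by the infusion it works the other way: the excess on lidocaine is spread over patients who never had the drug, and the two arms look more alike than they were among those treated. The trial intends to say something about safety, so the denominator behind that statement should be chosen deliberately and not inherited from the efficacy rule.

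**Working it through.** **Inputs from the article (Sample size calculation).** 57 evaluable patients per group, a 10% dropout allowance, 64 per group and 128 in total. The inflation step reproduces: 57/0.90 = 63.3, rounded up to 64, and 2 × 64 = 128. The 57 itself does not follow from the stated 20% of 43 mg (8.6 mg) and SD of 17 mg, which give 62 to 63 per group at two-sided 0.05. That is a separate matter with no bearing here.

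**Inputs that must be assumed.** The article gives neither adverse event rates nor the number never infused. For illustration, take true rates among treated patients of 30% on lidocaine (pL) and 15% on placebo (pC), with 1, 3 or 6 of 64 never infused in each arm. Six is close to the whole allowance (0.10 × 64 = 6.4). Equal shares are what one expects when allocation is concealed until theatre, although chance can make them differ.

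**Formulas.** Let f be the never-infused share.

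- Operation cancelled, no events recorded, same f in both arms: the rates become (1 − f)pL and (1 − f)pC. The difference is (1 − f)(pL − pC) and the rate ratio is unchanged.
- Operated on without the infusion, so carrying the background rate: the lidocaine rate becomes (1 − f)pL + f·pC and the placebo rate stays at pC. The difference is again (1 − f)(pL − pC).

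| Never infused per arm | f | Rates if cancelled | Rates if operated on uninfused | Difference, points (true 15.0) |
|---|---|---|---|---|
| 1 of 64 | 1.6% | 29.5% v 14.8% | 29.8% v 15% | 14.8 |
| 3 of 64 | 4.7% | 28.6% v 14.3% | 29.3% v 15% | 14.3 |
| 6 of 64 | 9.4% | 27.2% v 13.6% | 28.6% v 15% | 13.6 |

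The difference shrinks by the share f in both cases. The lidocaine rate itself depends on the case: with 6 of 64 it is 27.2% or 28.6%.

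**Against sampling error.** With 64 per arm the standard error of the difference is √(0.30 × 0.70/64 + 0.15 × 0.85/64) = 0.073, so the 95% half-width is 1.96 × 0.073, about 14 points. The dilution is 0.2 to 1.4 points.

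**Power for 30% v 15%.** It is 0.529 if all 64 per arm are infused. With 6 per arm never infused it is 0.479 by assignment and 0.490 among treated patients.

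**Upper limit for an event never seen on lidocaine.** The one-sided 95% limit is 1 − 0.05^(1/n). Counting all 64 gives 4.6%. Counting only the infused gives 4.8% for n = 61 (three never infused) and 5.0% for n = 58 (six never infused).

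**The case against.** The strongest reply is that this is an omission and so no error. The Data analysis section gives no test or denominator for adverse events; what it spells out concerns morphine, remifentanil and chronic pain. A safety set is commonly defined in a full protocol or analysis plan, and neither is shown. This stands in part: the missing definition is no fault. What remains is that the article states a general rule whose wording covers adverse events, so a treated set defined elsewhere would need an explicit exception to it.

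Other limits stand in full, and they rule out stronger readings that a reader might infer:

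- **That never-infused patients count as event-free.** No section says so. Surveillance in the recovery unit and on the ward covers all patients and is not tied to having been infused. Zero events fits cancelled operations only, and those should arise in both arms.
- **That about a tenth of the harm signal is lost.** The 10% is a dropout allowance for a 48-hour morphine outcome. Withdrawal or missing data after infusion fits it equally well.
- **That the bias always reassures.** The Background section makes opioid-related events such as nausea and sedation part of the case for lidocaine. If the event count includes these, the difference may favour lidocaine, and analysis by assignment then guards against overstating a benefit.
- **That syringe mix-ups misplace toxicity.** This is possible but hypothetical. The article suggests no rate of mix-ups, and it does not describe a record of syringe contents that would reveal one.

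**Conclusion.** The point holds as a minor one. The rule is stated without exception, adverse events are an outcome, and randomisation precedes infusion. If some patients are never infused, analysis by assignment therefore pulls the expected difference in infusion-related events towards zero by the never-infused share. This assumes equal shares in the two arms, or uninfused patients who carry the background rate.

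The share is unknown. A few percent seems likely because drug starts straight after induction, but that is a judgement and not a figure from the article. The dropout allowance is at best a rough ceiling. Over the range of 1 to 6 of 64 the relative shrinkage is 1.6% to 9.4%. No conclusion would plausibly turn on it at this sample size, and the primary outcome is unaffected.

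**What to change.** Qualify the intention-to-treat sentence in the Data analysis section. Keep the principle for morphine, remifentanil and chronic pain. Add that adverse events are summarised primarily in all patients who received any study infusion, grouped by treatment received where this is documented and otherwise by assignment, with the intention-to-treat summary alongside. Report the number randomised but never infused in each arm, so that the reader can see how little or how much the two summaries could differ.

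The cost is about one sentence and a second column in the adverse event table. The sample size and primary analysis do not change. Denominators for harm become slightly smaller and upper limits slightly less favourable (for example 4.8% in place of 4.6% if three of 64 were never infused and no event was seen). The choice should be fixed before the unblinding that the article places after the database freeze, so that results cannot influence it.

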### Sample size calculation

The study has been powered to detect a reduction of 20% of morphine consumption outcome between the study and placebo groups. Data from the head and neck surgery department of the Croix-Rousse Hospital permitted an estimation, in the absence of lidocaine administration, of a mean morphine consumption of 43 mg at day 2 (standard deviation 17 mg). With a statistical power of 0.80, 114 patients (57 per group) will be needed to demonstrate such a difference (Student’s *t* test). To compensate for a possible dropout of 10% of patients, it is planned to include a total of 128 patients (64 per group).

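### Randomisation is stratified by centre, but the primary analysis and two secondary analyses are unadjusted t tests; if consumption differs between centres, these tests are conservative and some power is lost

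*Protocol article*

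**What the plan says.** The Study design section states: "This study is a two-center, double-blind, randomized controlled prospective trial". The Randomization section adds: "Patients will be allocated by randomized complete block design, stratified by center, to one of the two groups". Centre is therefore the one declared stratification factor.

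For 48 h morphine, the Data analysis section says: "cumulative morphine consumption in the first 48 postoperative hours) will be performed using Student’s *t* test". For two of the secondary outcomes it says: "intraoperative remifentanil consumption as well as morphine consumption in the 24 postoperative hours will be compared between the two groups using Student’s *t* test". For chronic pain it says only that "The incidence of postoperative chronic pain will be compared between the two groups", without naming a test, and adds a logistic regression of associated factors. No test is named for adverse events.

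A further linear regression of 48 h morphine is planned. Its list begins: "The factors studied will be the type of surgery, tumor site, stage of cancer, duration of the surgery, NRS score upon arrival in the PACU". Preoperative analgesic use and high-dose intraoperative remifentanil complete the seven factors. Centre is not among them and treatment arm is not named.

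The Sample size calculation section also rests on a t test, with a mean of 43 mg and an SD of 17 mg taken from the head and neck department of one of the two hospitals.

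**The concern.** Balancing the arms within each centre removes any difference between centres from the true error of the treatment comparison. An unadjusted t test still counts that difference as residual noise. If centre predicts opioid use, the analysis reports less precision than the design delivers.

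The planned regression does not fill the gap. Its purpose is to find predictors, it omits centre, and it includes variables measured after randomisation that lidocaine could influence (pain score on arrival in the PACU, remifentanil use).

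What is at stake is efficiency and interval width, not validity. A real effect could be missed or reported with too wide an interval. A false positive does not become more likely by this route.

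**Working it through.** **Inputs from the article.** "The study has been powered to detect a reduction of 20% of morphine consumption outcome between the study and placebo groups", that is 0.20 × 43 = 8.6 mg; SD 17 mg; power 0.80; 57 evaluable per group, 64 enrolled. Significance is p < 0.05; two-sided is assumed.

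**Inputs assumed.** A gap of D mg between the two centre means, and a fraction p of patients in one centre. The article gives neither.

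**Step 1: the plan's own figure.** n per group = 2 × 17² × (1.960 + 0.842)² / 8.6² = 578 × 7.849 / 73.96 = 61.3, so 62 (63 by the exact t calculation). The stated 57 is not reproduced at 8.6 mg. A difference of 9 mg does give it: 578 × 7.849 / 81 = 56.01, rounded up to 57. The dropout step reproduces: 57 / 0.9 = 63.3, so 64 per group and 128 in total. At 57 per group and 8.6 mg, power is 77.1% (normal approximation) or 76.3% (exact t). This shortfall is a separate matter; here it only sets the baseline.

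**Step 2: formulas.** Let s be the SD within centres.
- True SE of the difference, arms balanced within centre: s√(2/n).
- SE that the t test estimates: √(s² + D²p(1−p)) × √(2/n).
- Inflation: k = √(1 + D²p(1−p)/s²).
- With the critical value 1.981 (112 df), actual type I error is 2P(T > 1.981k), and power is about Φ(8.6/SE − 1.981k). The centre-adjusted model has k = 1.

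**Step 3: 17 mg as a within-centre SD** (the natural reading, since it comes from one centre), equal centres. True SE = 17 × √(2/57) = 3.18 and 8.6/3.18 = 2.70. Adjusted power is Φ(2.701 − 1.981) = 76.4% for every gap.

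| Gap D (mg) | D²/4 | k | Type I error, t test | Power, t test | Power, adjusted | Loss (points) |
|---|---|---|---|---|---|---|
| 0 | 0 | 1.000 | 5.0% | 76.4% | 76.4% | 0 |
| 5 | 6.25 | 1.011 | 4.8% | 75.7% | 76.4% | 0.7 |
| 10 | 25 | 1.042 | 4.1% | 73.7% | 76.4% | 2.7 |
| 15 | 56.25 | 1.093 | 3.2% | 70.4% | 76.4% | 6.0 |

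Simulation under this reading agrees: for gaps of 8.6, 12.9 and 17 mg, unadjusted power is about 75%, 72% and 69%, against 76% to 77% adjusted.

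**Step 4: unequal centres.** With an 80:20 split, D²p(1−p) = 0.16D². At 10 mg, k = √(1 + 16/289) = 1.027, power is 74.7% and the loss 1.7 points. At 15 mg, k = √(1 + 36/289) = 1.060, power is 72.6% and the loss 3.8 points.

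**Step 5: 17 mg as a total SD**, equal centres, so s² = 289 − D²/4. Simulated power, unadjusted against adjusted, is 77.1% against 77.8% at 5 mg, 77.0% against 79.6% at 10 mg, and 78.6% against 84.5% at 15 mg. Type I error of the t test is 4.3%, 4.1% and 2.7%. The losses (0.7, 2.6 and 5.9 points) match Step 3, but the absolute powers are higher because a larger gap then implies a smaller within-centre SD.

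The article gives no mean or SD for remifentanil or 24 h morphine, so no size can be computed for those two outcomes.

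**The case against.** The strongest reply is that no centre difference is documented. The Intervention plan section says "a standardized general anesthesia and postoperative care protocol will be followed in each center", and the postoperative sections set one morphine titration, PCA and acetaminophen regimen for all patients. The 10 and 15 mg gaps exceed the 8.6 mg treatment effect itself, and at 5 mg the loss is under one point. This stands: the loss is conditional and may be nil. It does not show that the centres are alike, because care standardised in each centre need not be identical across centres, and a wide range of procedures allows case mix to differ.

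A second reply is that an unseen analysis plan may add centre. That is possible, but the article does not leave the test open: it names Student's t test for the analysis and again for the sample size.

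A reader might also infer that every secondary comparison is an unadjusted t test. The article ties only remifentanil and 24 h morphine to that test. The missing test names for chronic pain and adverse events are detail that an article commonly leaves to the full protocol.

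**Conclusion.** The mismatch is real: centre is the stratification factor, and it is absent from the primary analysis and from the two secondary t tests. The consequence is conditional and modest. If the centres do not differ, nothing is lost. With 57 per group, a gap of 5 mg costs under 1 point of power, 10 mg about 1 to 3, and 15 mg about 4 to 6, the upper ends applying to equal centres. Type I error falls to about 4.5%, 4% and 3%. These figures rest on assumed gaps, a two-sided 5% level and arms balanced within centre.

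Two stronger readings should be resisted. One is that power is certainly lost; the documents give no centre effect. The other is that adjusting for centre would restore 80% power or better. That follows only if 17 mg is a total SD over both centres, whereas the article takes it from one hospital. On that basis adjusted power stays near 76%, and adjustment only prevents a further fall. Nor is this a bias or false-positive problem. It is a free improvement.

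**What to change.** Before unblinding, specify the primary analysis as a linear model of 48 h morphine on treatment arm and centre, and report the adjusted mean difference with its 95% confidence interval. Use the same model for intraoperative remifentanil and 24 h morphine. Keep the unadjusted t test as a supporting analysis, and keep the seven-factor regression separate as an exploratory search for predictors.

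The cost is a few lines of analysis-plan wording and one degree of freedom. No new data are needed, and if the centres turn out alike the result is essentially unchanged.
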